### Recruitment

To achieve Aim 1, we will recruit 300 women (age 18–24 years, *n* = 150 in Maryland and *n* = 150 in Oregon), enrolled at least part-time in college, who self-report current or past 6-months experience of physical violence, sexual violence, psychological abuse, or stalking by a dating/intimate/ex-intimate partner. Participants will be randomized to the intervention (MyPlan App) or the control group (generic IPV resource App). Outcomes for survivors will be collected by self-report at baseline, 6, and 12-months during the App session using validated measures. To achieve Aim 2, we will recruit 300 students (male or female) ages 18–24 years old (*n* = 150 in Maryland and *n* = 150 in Oregon) who are: 1.) enrolled at least part-time in college and 2.) report having a female friend with current or past 6-months experience of physical violence, sexual violence, psychological abuse, or stalking by a dating/intimate/ex-intimate partner. Friends of survivors will be randomized to the intervention (MyPlan App friend component) or the control group (generic friend IPV resource App). Outcomes (awareness of IPV, decisional conflict, supportive behaviors and confidence to intervene) for friends will be collected by self-report at baseline, 6- and 12-months post App session using validated measures. Eligible participants will also need to have safe access to a computer or smartphone with internet (“safe” meaning access to a device an abusive partner doesn’t have access to). A safe email address that an abusive partner does not have access to is also required to receive study related information.

Participants will be recruited through multiple strategies proven successful in our recruitment and retention of diverse populations in previous studies. These include partnerships with campuses to post advertisements for the study on campus social media, student listservs, etc. and to hang recruitment flyers in locations where students may seek assistance (campus clinics, student affairs office, etc.) or gather for support (student center, sororities, counseling centers). Advertisements on websites such as Craigslist and on community agency websites or social media may also be utilized.

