### Accessing the App

Upon obtaining informed consent, collecting safety contact information, enrolling participants and entering their information into the secure study database, participants will be randomly assigned to intervention or control groups using a computerized stratified blocked randomization scheme. Randomization occurs automatically at the time of enrollment via a randomization algorithm. Participants will be randomized to complete either the MyPlan Intervention App or the Generic IVP Resource App (control). Stratification is based on state of residence (Maryland or Oregon), type of participant (friend/survivor), survivor having children (child/no child in home), and type of school (two year technical school, community college, four year state college or university, four year private college or university, or other). Blocked design will ensure that the proportion of women/friends in Maryland and Oregon assigned to one group or the other remains relatively constant throughout the study. Once the participant is randomized, an automated email from the RA will be sent to the participants’ safe email address containing the assigned (intervention or control) study App access instructions. The participant will have two options to access the App. The first option is to download the App to their smartphone from one of the major U.S. App stores, where it will be posted as a free App available to anyone with a smartphone. Once downloaded, the App is user and password-protected, like a bank App, preventing others not enrolled in the study (e.g., partners) from opening the App. The second access option is to use the smartphone’s or computer’s Internet browser to access a web-based version of the App via the study website. With either mode of access, users will enter an assigned username and password the first time the App is accessed. They will also be instructed to set a security PIN code as the primary means to access the app once logged in. Users can define any 4 digit code to be the PIN and if they need to reset the PIN, must first log out and then back in using their username and password. Participants will be instructed to remove the App once they have completed the session if unsafe to have on their device, though warned that it is not currently possible to delete apps from a purchase history. Data collected from participants is labeled as either study data or personal identifiers. In order to ensure the highest protection of privacy and security, all personal identifiers (only collected at study enrollment) are saved in a physically separate database in a HIPAA compliant network environment. Study data and personal identifiers are never combined during the course of the study. Detailed safety procedures have been developed and are explained in the Risks section.

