### Intervention effectiveness

Residualized change regressions will be used to test for significant differences between the intervention/control groups in change in decisional conflict. Change on the Decisional Conflict subscales, e.g., values or priorities clarification from pre-to post-use at the first session will be the dependent variable. Group (intervention vs. control), baseline decisional conflict and potential confounding variables for which intervention and control groups differ at baseline will be included in the model as independent variables. Longitudinal multilevel models will be used to examine change over time in women’s safety behaviors (percent of safety behavior tried that a survivor found helpful), IPV (measured by the CAS) and substance use (measured by AUDIT and DAST). Time (e.g. baseline, 6 months, and 12 months) will be used as a level 1 predictor of the dependent variable. The level 1 model yields an intercept and slope parameter for each person. The intercept reflects the baseline value on the dependent variable and the slope reflects the rate of change across time on the dependent variable. Group will be used as a level 2 predictor of slope parameter. Finding the group is a significant predictor of the level 1 slope parameters means that individual change over time differs for intervention and control groups. Potential confounding variables for which intervention and control groups are significantly different at baseline will be entered as level 2 covariates predicting individual change.

The same set of analyses described above will be used to examine change in friend’s awareness of IPV, decisional conflict, safety behaviors and confidence to intervene.

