### Mediation analyses

Additionally, change in decisional conflict will be tested as a mediator of the relationship between the intervention and safety behaviors at 12 months for both survivors and friends of survivors using a series of regressions. Sobel’s test will be used to estimate the mediation effect. The product coefficient Approach associated with the Sobel’s test has been found to be a powerful method for estimating indirect effects [59]. The mediation effect and associated boot-strapped 95 % confidence intervals will be estimated. Separate analyses will be conducted for the women and friends. A similar approach will be used to test safety behaviors at 12-months as a mediator of the relationship between the intervention and change from baseline to 12-months in IPV for the women and confidence to intervene for friends.

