### Statistical power

We based the power analysis on a repeated measures ANOVA, but propose to use multilevel modeling for the analyses which allows all cases with missing data to be included in the analyses. We do not have adequate estimates of the within and between variance to estimate power for the multilevel model directly. However, in general multilevel model approaches are more powerful than repeated measures ANOVA. We have powered the study at the .90 level rather than .80 as we want to have adequate sample sizes to conduct exploratory analyses of the moderators of the intervention effect if necessary. Since the primary purpose of the safety intervention is to increase safety-seeking behaviors, the power analysis is based on an effect size calculated from the results from a previous IPV intervention [36]. These investigators evaluated the effect on safety-seeking behaviors of a telephone intervention compared to usual safety services in Spanish-speaking and English-speaking women who obtained restraining orders. The effect size, f, was computed to be 0.58, and according to Cohen’s conventions, this represents a medium effect size. Using means obtained from the telephone intervention study, this effect size is equivalent to a mean change from baseline to follow-up of 14.4 % for the intervention group compared to a change of 10.4 % in the control group from baseline to 12-months. Assuming an autocorrelation of 0.3, 300 participants in the intervention and 300 participants in the usual safety services group provide 0.99 power to detect a significant group by time interaction at the 0.05 alpha level. Assuming an attrition rate of 20 % and the same parameters as above, the study will have 0.99 power to detect a significant effect of the intervention. Even in a scenario where the attrition rate would be 37.5 %, the study would still have adequate power greater than .90 to detect a significant group by time interaction. Our prior work in this area suggests that 20 % is a reasonable attrition rate and we have successfully used multiple strategies to reduce attrition as described above.

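### The power statement uses 300 participants per arm, but survivors and friends are separate populations of 300 in total, so no planned comparison has more than about 150 per arm

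*Protocol article*

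**What the plan says.** Recruitment section: "To achieve Aim 1, we will recruit 300 women", and, separately, "To achieve Aim 2, we will recruit 300 students (male or female"). For survivors, "Participants will be randomized to the intervention (MyPlan App) or the control group (generic IPV resource App"); friends are likewise randomised between the friend versions of the two apps. The 150s given in that section are numbers per state (Maryland and Oregon), not per arm.

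Accessing the App section: randomisation is stratified, and one of the factors is "type of participant (friend/survivor").

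Outcomes section: survivors are assessed on helpful safety behaviours and decisional conflict. Friends are assessed on awareness, confidence to intervene, supportive behaviours and conflict about helping.

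Intervention effectiveness section: after the survivor models are set out, "The same set of analyses described above will be used to examine change in" the friends' own outcomes. For mediation the separation is explicit: "Separate analyses will be conducted for the women and friends".

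Statistical power section: "300 participants in the intervention and 300 participants in the usual safety services group provide 0.99 power" for the group-by-time interaction at alpha 0.05, with an autocorrelation of 0.3 and an effect of 0.58 taken from an earlier telephone intervention. The section repeats 0.99 for 20% attrition and says that at 37.5% attrition "the study would still have adequate power greater than .90 to detect a significant group by time interaction". It gives the wish to explore moderators as the reason for powering at .90 rather than .80.

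**The concern.** Three hundred per arm exists only if survivors and friends are pooled into one comparison of 600. The document plans no such comparison. The two groups are randomised in different strata and measured with different instruments, and the powered outcome, safety-seeking behaviour, is a survivor outcome whose assumed effect came from a study of abused women.

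The three stated powers therefore describe an analysis that the trial will not run. A reader who relies on them will overestimate the precision of each aim and the room left for moderator analyses, which are planned within each aim.

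**Working it through.** **Inputs.** From the Statistical power section: effect 0.58, autocorrelation 0.3, alpha 0.05, attrition 20% and 37.5%, 300 per arm. From the Recruitment section: 300 survivors and 300 friends, each set randomised to two arms. Assumed here: 1:1 allocation and a two-sided test.

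**Arm sizes.**

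| Attrition | As stated | Each population |
|---|---|---|
| none | 300 | 300 / 2 = 150 |
| 20% | 300 × 0.8 = 240 | 150 × 0.8 = 120 |
| 37.5% | 300 × 0.625 = 187.5 | 150 × 0.625 = 93.75, about 94 |

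**Readings of 0.58.** The section labels it f but calls it medium by Cohen's conventions, and it gives no SD. Three readings were tried:

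- (a) A literal f in a repeated-measures ANOVA interaction: noncentral F with λ = f²·N·m/(1 − ρ), ρ = 0.3, and m = 2 or 3 occasions.
- (b) A standardised difference d on the change score: power = Φ(d·√(n/2) − 1.96), n per arm.
- (c) A standardised difference in raw SD units. The change score then has SD √(2(1 − 0.3)) = √1.4 = 1.183, so d on change = 0.58 / 1.183 = 0.490.

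**Reproducing the plan's figures at 300 / 240 / 187.5 per arm** (stated: 0.99 / 0.99 / above .90):

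- (a) 1.000 / 1.000 / 1.000
- (b) 1.000 / 1.000 / 0.9999
- (c) 1.000 / 0.9997 / 0.997

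All three agree with the stated figures if those are taken as lower bounds.

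**At the real sizes, 150 / 120 / 94 per arm:**

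- (a) 1.000 / 1.000 / 1.000
- (b) 0.999 / 0.994 / 0.978. Example at 120: 0.58 × √60 = 4.493; 4.493 − 1.96 = 2.533; Φ = 0.994.
- (c) 0.989 / 0.967 / 0.919. Example at 120: 0.490 × √60 = 3.797; 3.797 − 1.96 = 1.837; Φ = 0.967.

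**Smallest difference detectable with 0.90 power,** in change-score SDs: (1.960 + 1.282) / √(n/2).

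- 240 per arm: 3.242 / √120 = 0.30
- 120 per arm: 3.242 / √60 = 0.42
- 150 and 94 per arm: 0.374 and 0.473

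Halving the sample raises the detectable difference by √2, about 41%, at any given attrition rate.

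**The case against.** The strongest reply is that the error changes little. On the protocol's own effect of 0.58, every reading tried keeps power above the .90 target at the real arm sizes, even with 37.5% attrition. Reading (c) at 150 per arm (0.989 / 0.967 / 0.919) also lies close to the stated pattern, so the sentence may be a wording slip for 300 in total. The planned multilevel models keep partly observed participants, so treating attrition as complete loss is cautious. The moderator analyses are already called exploratory, so nothing needs relabelling there. The sentence on separate analyses belongs to the mediation section, and the allocation ratio is not stated.

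Most of this stands. The separation of the two populations does not depend on the mediation sentence, because the strata, outcomes and effectiveness models already establish it. The document does not settle whether the figure is a slip, and a slip would need correcting as well.

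A reader might go further and infer that real power is below .90. One route is to solve backwards from the stated powers. Taking 0.90 as exact at 187.5 per arm gives d = 0.335, and so 0.83 / 0.74 / 0.63 at 150 / 120 / 94. But d = 0.335 gives only 0.984 at 300 and 0.956 at 240 per arm, which contradicts the stated 0.99s. Taking 0.99 as exact at 240 per arm gives d = 0.391, and so 0.92 / 0.86 / 0.76. That treats a figure that may well be a ceiling as exact, and neither value of d is in the document.

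Another route starts from the quoted changes of 14.4% and 10.4%, a difference of 4 points. No SD is given, so power can only be shown over assumed values. At 150 / 120 / 94 per arm, a change SD of 10 gives 0.93 / 0.87 / 0.78, and an SD of 15 gives 0.64 / 0.54 / 0.45. By comparison, 0.58 implies a change SD of 4 / 0.58 = 6.9 under reading (b), or 6.9 × 1.183 = 8.16 under reading (c). This is a question about the effect size, separate from the doubled sample.

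**Conclusion.** The point holds as an error in the stated sample-size basis. No planned test has 300 per arm. Under 1:1 allocation each aim has about 150, falling to 120 and about 94.

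The document does not support the conclusion that the trial is underpowered. With 0.58 read as a standardised difference, more than .90 holds throughout. The one stated figure that may fail noticeably is the 0.99 at 20% attrition, which is 0.967 under reading (c). What is clearly overstated is precision: after 20% attrition the detectable difference is about 0.42 SD rather than 0.30 SD, so the margin claimed for moderator analyses is smaller than implied.

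These results rest on equal allocation, a two-sided 0.05 test, a two-sample approximation for (b) and (c), and the protocol's own 0.58.

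**What to change.** Replace the 300-per-arm statement, or correct it to 300 in total if that was meant. Report power separately for survivors and for friends at 150, 120 and 94 per arm. State the allocation ratio, say whether 0.58 is f or a standardised difference and which SD it refers to, and add the minimum detectable difference at 120 per arm.

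The cost is one rewritten paragraph and a slightly less favourable stated power. Enrolment, randomisation and the planned models do not change.

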## Risks and safety

The research team is well aware that questioning women/friends about partner violence is a sensitive topic that raises important questions about safety [57, 60]. Potential risks to participants are loss of confidentiality, time involvement, fatigue, distress and embarrassment because of the nature of some of the questions, anxiety, depression, and potential retaliation from the abusive partner if they learn of her/his participation in the study. As compared to the risks of a person seeking services and communicating with domestic violence services in the community, and viewing domestic violence safety information on a website or App, the risks are no greater. These risks will be minimized by developing and training study staff on safety protocols. All participants will be informed about the potential risks in participating and measures to take to protect one’s self, including safety measure for smartphone/internet use. All participants will be notified that they can withdraw from the study at any time without penalty. While participants’ safety cannot be completely guaranteed, we feel that with our safety procedures there is minimal safety risk. Although the circumstances of abuse may be distressing for survivors and friends to discuss, traumatized persons generally find expression of feelings useful. The research plan was developed with deliberate attention toward minimizing the risk of harm to abused women and friends of abused women. Following these safety protocols in previous online research, no adverse events were reported.

### Protection against risk

Measures to protect the study participants  will follow the guidelines set forth by the Nursing Research Consortium on Violence and Abuse (NRCVA) [61]. We are extremely concerned about safety, and this concern underlies the rationale for our procedures and research. Confidentiality is considered primary to this study protocol. Implementing important safety procedures for the internet and handling study data will serve to protect participants from harm. During the study, participants may stop at any time. All participants and those not eligible for participation will be offered information on safety resources for IPV. No information will be given out to anyone outside the research team about whether a particular person participates in the study. The study will generally be referred to as a “College Safety Study”. Trained research staff will conduct all aspects of the study.

All research team members will be trained using the approved protocol. Research team members will complete online human subjects research training through their institution. Further, all research team members will receive and review documentation on policies and procedures for managing and reporting adverse events that might arise during the study. The study investigators, who have many years of experience in the field of IPV and intervention research, will train all research staff prior to their involvement in the study. The training will include sensitization to the experience of abused women/friends, recruitment and retention protocols and scripts, safety issues and response (including protocols for on-line and telephone contacts with participants as well as handling and reporting of suicidal ideation, child abuse or harm to others), maintaining confidentiality of all research participants, intervention protocols and fidelity to protocols as well as issues related to informed consent. All research staff members will be provided a training manual as a reference. Refresher training and assessment will occur at least annually in order to prevent drift from these research protocols for safety.

Risk will also be minimized by providing participants with choices to allow the participant to decide the safest way for them to communicate with the study. Other safety considerations will be to discuss with participants the potential for abusive partners to monitor online/phone activities and ensure participant has a safe email address and safe device they can access in order to participate, making sure participants are aware of the type of information we will send them via email, asking them how they prefer to be communicated with and if there are any safety instructions for each mode of communication, providing participants with information on methods of protecting their privacy on their devices (smartphone/computer), and storing the intervention related data which will be identified only by a study ID# on a separate database from the enrollment data which will include contact information. Potential participants will be provided with a description of the risks or discomforts and the anticipated possible benefits. Additionally, to minimize the linkages of a participant to the study, the study is requesting a waiver of signed consent and will conduct oral consent in lieu of requiring a document about a relationship violence study containing a signature.

### Safety mechanism for online data collection

A link, username, and password to the secure study App will be emailed to the safe email provided by participant. The App measures and intervention will not collect any protected health information (PHI) from the participant. There is risk that an abusive partner could uncover the trail of sites visited by the participant and discover the purpose of the study. This risk will be discussed in detail with all participants and all participants will be given instructions in the email with the survey web link for safe internet use including using a computer/phone their partner doesn’t have access to, setting strong password protection for all devices, accessing “private” browsing, the limitations of deleting Apps completely from purchase histories, and covering up tracks on web browsers’ history files.

### Safety mechanisms to ensure data privacy

All persons with access to data (PI, co-investigators, RAs, consultants) will rigorously follow procedures to ensure confidentiality of data. All data will be secured in a password-protected, secure server and database. Contact information (PHI) will be collected for the participants separately and maintained securely in the study database on our secure server. No persons other than the investigators and study RAs will have access to contact information. Contact information for participants will be destroyed following completion of the study. Only a single file will contain PHI linking subject-identifying information (names) with study ID code. These sensitive files containing identifying information will be encrypted. This additional security requires the end-user to have both access authority and a password for the encryption/encapsulation. All other study materials and files will only include the study ID code.

